### 3.2. Plan of Analysis

Primary and secondary endpoints and the statistical plan of analysis are described in Table 1. Five subgroups for analysis are declared: manufacturing site (Spain, France S1, France S2, Germany, and Italy); anatomical site: femur, humerus, and tibia; time (months) since acute fracture; smoking habits (yes/no); and sex (female/male). For these, Fisher's exact test for categorical variables, *t*-test or one-way ANOVA for Gaussian distributed variables, Mann–Whitney test and Kruskal-Wallis for non-Gaussian continuous variables will be used.

The plan of analysis will be tested in the following two populations of analysis: (a) modified full analysis set (mFAS) that will include all patients who have received treatment; (b) per protocol population (PP) that will include those patients in the mFAS set without major protocol deviations. Procedures to account for missing or spurious data will include patients whose information on consolidation is unknown at the end of the trial and will be considered failures, irrespectively, to the drop-out reason. With regard to the radiological consolidation, the baseline value will be used to impute the missing case; in case of treatment-related missing data, the missing case is not imputed otherwise. No formal imputations will be performed for the rest of variables, and the analyses will be based on the Available Data Only (ADO) approach.

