#### 2.5.2. Bone Marrow Mesenchymal Stem Cells + Biomaterial Implantation

First, the bone marrow will be harvested under loco-regional (epidural, spinal) or general anaesthesia. Bone marrow will be aspirated from the anterior or posterior iliac crests, after insertion of a bevelled needle (6 to 8 cm in length and 1.5 mm in internal diameter) into the spongy bone, and transferred into a 20 mL plastic syringe with 1 mL of heparin. At a given depth, the needle will be turned 45° to reorient the bevel during successive aspirations, so that the largest possible space is aspirated. After one full turn, the needle will be moved 1 cm toward the surface through the same insertion site, and aspirations will again be performed, with the needle always turned 45° after each aspiration. The marrow will be aspirated in small fractions (3–4 mL) to reduce the degree of dilution by peripheral blood. A total of 30–35 mL of bone marrow will be aspirated. If necessary, two or three perforations will be performed, through the same skin opening, into the iliac crest, with the perforations spaced approximately 2 cm from each other to avoid dilution by aspiration in the previous hole. All aspirates will be pooled in plastic bags containing an anticoagulant solution. The bone marrow will be then forwarded to the associated GMP facilities. The final product of expanded MSCs will be manufactured according to GMP rules using aseptic procedures and disposable sterile single-use supplies for all product contact steps. The whole process will be conducted in accordance with written procedures and each step will be recorded on batch. All manipulations involving the initial preparation of cells, cell culture, and cell packaging will be performed in clean rooms of appropriate class of air cleanliness. The batch production records for each lot require documentation and confirmation signatures that the procedures have been followed. Briefly, MSCs will be cultured and expanded using alpha MEM medium supplemented with PL [19]. Cells will be conditioned in a syringe for injection. The final product will consist of fresh, autologous bone marrow MSCs, expressing the markers CD90, CD73, CD105 and negative for CD14 and CD45 and HLA class II, with a 90% viability rate, at a dose of 100 × 10^6^ or 200 × 10^6^ cells (G2a and G2b) suspended in 5% human albumin up to 10 mL (the delivery contains two syringes of 5 mL each).

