Secondly, the conduction of the surgery will be the same as for bone autograft, except for the implantation of the composite (hBM-MSCs + biomaterial). The mixture will be prepared in the operating room as per protocol [20] and placed in the previously prepared area to be grafted. Each 5 mL cell product syringe is mixed with 5 cc of biomaterial (1-2 mm MBCP+ granules) filling the intergranular pores. The final mixture of the biomaterial and cells has a pasty consistency and it will be preferably introduced within the gap of the nonunion. Circumferential use of the material will only be performed when the bone gap is filled.

In both cases, a stable fixation of the fracture will be required. The use of an osteosynthesis system may include static or locked nail, locked or unlocked bone plate with screws, and/or external fixator (including the Ilizarov system) when other means are not adequate. Furthermore, the surgical technique will be reevaluated postoperatively by the clinical trial committee, to confirm the predefined criteria of a satisfactory surgical procedure (stable fixation and adequate augmentation) to validate the analysis of the case as per protocol. These criteria include absence of major complications after the procedure (intraoperative fracture, deviation, inadequate reduction, or other surgical gestures or interventions, except fibular osteotomy if required for compression or reduction of a tibial nonunion), presence of sufficient biomaterial or graft (filled nonunion gap, presence of sufficient graft/material in the fracture compression side and not in the tension side), and sufficient fixation (detecting immediately after surgery what could be considered an unstable fixation or unstable nail or other suboptimal techniques).

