Difficulties are encountered to define the sample size, the randomization procedure, and the study design due to the scarcity of comparable studies. A multicentric, randomized study was planned to ascertain that, having standardized the ATMP in four countries (France, Germany, Italy, and Spain), patients could receive analogous treatment from different GMP facilities in different hospitals. First, this requires agreement of the national regulators, and a voluntary harmonization procedure (VHP) was launched within the European Union [35]. Second, stratification by production centre has been planned for the randomization procedure, and this will enable to similarly assess cell production in all centres.

The sample size calculations have been based on success rates with ICA as the control on bone healing multicentric trials [8]. Scarcity of references (both for controls and technology under evaluation) is observed in the literature. Of note, no direct head-to-head comparison in a well-designed randomized clinical trial has been previously conducted with ICA and MSCs. In this scenario with uncertainties in the final success rates and in the final delta of superiority, it is also noted that very small rate changes in those assumptions may have an impact in the actual statistical power. However, clinical relevance of the potential superiority of the technique would not be clearly defined unless the success rate is clearly higher. Furthermore, other reasons for failure besides the augmentation with the ATMP need to be excluded by the clinical trial committee. Foreseen reasons of failure unrelated to the ATMP include unstable fixation or other mechanical issues, inappropriate placement of the biomaterial with cells or the bone autograft (on-lay apposition instead of the recommended in-lay application), or intraoperative complications (intraoperative fractures or other distortion). Those cases will not be evaluated by PP although ITT analysis will be performed. Justification of the noninferiority of the lower versus the higher dose of hBM-MSCs is also a potential limitation of the study. A pragmatic approach was agreed in a noninferiority margin of 10% consolidation rate based on the differences between ICA controls and technologies designed to enhance bone healing in retrospective [26] and prospective [8] studies. This difference of 10% could be considered clinically irrelevant.

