SO4: to compare pain with and without weight bearing using the G1 versus G2 and G2a versus G2b treatment arms	Pain score using the Numeric Rating Scale from 0 to 10, when 0 = no pain at all and 10 = worst pain ever	At baseline and 6, 12, and 24 months after surgery	Fisher's exact test Mann–Whitney test

SO5: to compare the rate of further surgical intervention at the callus site between G1 versus G2 and G2a versus G2b treatment arms	Further surgical intervention at the callus site is considered when nail replacement, plate replacement, or replacement of all components of the previous surgery are performed.	At 6, 12, and 24 months after surgery	Fisher's exact test

SO6: to compare the early and global complication rate between G1 versus G2 and G2a versus G2b treatment arms	Early (<3 months) and global complications included the following: (i) AE related to the product application process (surgical or other, including BM or ICA harvesting) (ii) Local heterotopic ossification (iii) Local bone resorption (iv) Local osteolysis (v) Local and general infection (vi) Vascular problems (ischemia, phlebitis) (vii) Neurological problems (viii) Unexpected events (e.g., hypersensitivity, immunological, and toxic) (ix) AE related to concomitant medication (e.g., anaesthetics)	At 6, 12, and 24 months after surgery	Fisher's exact test

SO7: to assess the safety of autologous hBM-MSCs between the G1 and G2 treatment arms	Safety understood as early or global complication rates and SAE rates, related to the use of hBM-MSCs	At 6, 12, and 24 months after surgery	Fisher's exact test

SO8: to identify the factors associated with bone regeneration between G1 versus G2 and G2a versus G2b treatment arms	Association outcomes (*β*, RR)	At 6, 12, and 24 months after surgery	Log-binomial regression model and mix model for repeated measurements^∗∗^

SO9: to compare the physical and mental health status between G1 versus G2 and G2a versus G2b treatment arms	SF-36 Health Survey score	At baseline and 6, 12, and 24 months after surgery	*t*-test or Mann–Whitney test

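### Neither population in section 3.2 fits the complication endpoint: mFAS leaves out marrow-harvest events in patients never implanted, and PP excludes major procedural complications

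*Protocol article*

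**What the plan says.** Section 3.2 refers to Table 1 for the endpoints and their analyses, then states: "The plan of analysis will be tested in the following two populations of analysis". The first is the "modified full analysis set (mFAS) that will include all patients who have received treatment". The second is the "per protocol population (PP) that will include those patients in the mFAS set without major protocol deviations". Table 1 includes SO5 (further surgery at the callus site), SO6 (complications) and SO7 (safety of the cells), each with Fisher's exact test. No other population is attached to these three objectives.

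On the events:
- Table 1, SO6 counts "AE related to the product application process (surgical or other, including BM or ICA harvesting").
- Table 1, SO7 reads: "Safety understood as early or global complication rates and SAE rates, related to the use of hBM-MSCs".

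On the timing of harvest:
- Section 2.5.2, cell arms: "First, the bone marrow will be harvested under loco-regional (epidural, spinal) or general anaesthesia". The marrow then goes to a manufacturing facility, is expanded, and is implanted at a later operation.
- Section 2.4, control arm: the graft is taken during the nonunion operation itself.

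On PP:
- Section 2.5.2 has the clinical trial committee judge after surgery whether a case is valid for the per protocol analysis. "These criteria include absence of major complications after the procedure (intraoperative fracture, deviation, inadequate reduction, or other surgical gestures or interventions", with an exception for fibular osteotomy.
- The Discussion lists unstable fixation, misplaced graft or biomaterial, and intraoperative complications, and says: "Those cases will not be evaluated by PP although ITT analysis will be performed".

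**The concern.** SO6 is written to capture the harms of the whole treatment pathway, harvesting included. The populations are written for efficacy: one starts at treatment received, the other at a technically satisfactory operation. Used for SO6, the first can miss an event that the endpoint names, and in the cell arms only. The second conditions on the absence of part of the outcome being compared.

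At stake is the comparison of complications between G1 and G2 in an open trial. Its introduction gives donor-site morbidity of iliac crest graft as one reason to look for an alternative. The harvest burden of that alternative should therefore be counted in full.

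**Working it through.** The plan states no figure that depends on the safety population, so there is nothing to reproduce. The check compares the definitions and then uses arithmetic to find direction and size.

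**Step 1. Is a harvest-only patient in mFAS?** Table 3 describes the cell-arm treatment as expanded cells with biomaterial, given locally at the nonunion surgery. A patient whose marrow was aspirated but who never reached implantation has not had that. Non-implantation is possible: section 2.5.2 sets marker, viability and dose requirements for the product, and the Discussion describes its release criteria as strict. PP is a subset of mFAS, so such a patient is in neither set. G1 has no separate harvest before the operation and so has no counterpart to this loss.

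**Step 2. Effect on the cell-arm SO6 rate in mFAS.** Input from the documents: 72 cell-arm patients (section 3.1.1). Assumptions: m patients harvested but not implanted, complication rate c in implanted patients, rate h in harvest-only patients.

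- mFAS rate = c
- Rate in all harvested patients = ((72 − m)c + m·h)/72
- Expected events lost from mFAS = m·h

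With c = 20%:

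| m | h | Rate in all harvested | Events lost |
|---|---|---|---|
| 2 | 5% | (14.0 + 0.1)/72 = 19.6% | 0.1 |
| 2 | 40% | (14.0 + 0.8)/72 = 20.6% | 0.8 |
| 7 | 5% | (13.0 + 0.35)/72 = 18.5% | 0.35 |
| 7 | 20% | (13.0 + 1.4)/72 = 20.0% | 1.4 |
| 7 | 40% | (13.0 + 2.8)/72 = 21.9% | 2.8 |
| 14 | 5% | (11.6 + 0.7)/72 = 17.1% | 0.7 |
| 14 | 40% | (11.6 + 5.6)/72 = 23.9% | 5.6 |

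Harvest-only patients leave the denominator as well as the numerator. The mFAS rate is too low only if h exceeds c. If h equals c it is unchanged, and if h is below c it is too high. The harvest-only events themselves are lost in every case.

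**Step 3. SO5 and SO7 in mFAS.** SO5 counts replacement of components from the previous surgery. Harvest-only patients have had no trial nonunion surgery, so including them would tend only to dilute the rate. SO7 is tied to use of the cells, and a patient who received none can contribute little. Both are little affected.

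**Step 4. PP.** Assume a share q of mFAS patients has a major procedural complication that counts under SO6 and removes the case from PP. Let r be the rate of other complications among the rest, and suppose PP makes no other exclusions.

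- mFAS rate = q + (1 − q)r
- PP rate = r

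With q = 5% and r = 5%: 0.05 + 0.95 × 0.05 = 9.75% in mFAS (9.8% rounded), 5% in PP. With q = 15% and r = 10%: 0.15 + 0.85 × 0.10 = 23.5% in mFAS, 10% in PP. The PP rate is lower whenever q is above zero and r is below 100%.

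A difference between arms in q disappears. With r = 5% in both arms and q = 15% in one and 5% in the other, mFAS shows 0.15 + 0.85 × 0.05 = 19.25% against 9.75%, and PP shows 5% against 5%. This holds whichever arm has the higher q.

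**Step 5. The populations against each other.** Section 3.2 lists mFAS and PP. The Discussion promises an ITT analysis for cases left out of PP, without defining it or linking it to safety. The two places do not agree.

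**The case against.** The strongest reply is that a journal article condenses the protocol. A separate safety set, and the assignment of populations to endpoints, are often left to the full protocol or the SAP. On this view mFAS is close to a conventional treated-patient safety set, and nothing says that PP will carry the safety conclusions. Part of this stands: the absence of a named safety set would not by itself be a finding. The article does, however, state a rule for the whole of Table 1, and that rule does not fit an endpoint in the same table.

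Second, treatment received is not defined. Section 2.4 counts expansion as part of the experimental treatment, and section 2.5.2 makes harvest its first step, so a harvest-only patient might be meant to be in mFAS. Exclusion is therefore an inference, although Table 3 supports it. The text still has to settle the matter.

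Third, a reader might infer stronger claims that the documents do not support:
- *Safety is analysed only in mFAS and PP.* The Discussion mentions an ITT analysis, although it is undefined and not tied to safety.
- *Complication, reoperation and SAE rates are all understated.* Step 2 shows that the mFAS complication rate can move either way, and step 3 that SO5 and SO7 are little affected.
- *PP removes SO5 reoperations by definition.* The reference to other surgical gestures or interventions, with its fibular osteotomy exception, reads as acts at the index operation and not as later nail or plate replacement.
- *PP favours the cells.* Its surgical criteria apply to both arms, and the Discussion gives them an efficacy purpose. Most SO6 items, such as infection or heterotopic ossification, are not named as PP exclusions.

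**Conclusion.** The point holds in this form. The stated populations do not fit SO6. On the natural reading, harvest events in cell-arm patients who are never implanted fall outside mFAS although SO6 names them, and G1 has no such loss. PP complication rates are lowered by construction in both arms, which can hide a difference between arms in either direction. Section 3.2 and the Discussion disagree on which populations exist.

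The size cannot be fixed from the documents. They give no rate of non-implantation or of complications, and the 5% loss in section 3.1.1 is not a production-failure rate. With 2 to 14 of 72 patients not implanted and harvest-only complication rates of 5% to 40%, 0.1 to 5.6 expected events are lost. Against an assumed mFAS rate of 20%, the rate in all harvested patients lies between 17.1% and 23.9%. For PP, with q of 5% to 15% and r of 5% to 10%, rates of 9.8%–23.5% fall to 5%–10%.

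The plan should be corrected on this point. It does not bear on the primary efficacy endpoint or its sample size.

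**What to change.** In section 3.2:

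1. Add a safety set: all randomised patients in whom any trial procedure was started, marrow harvest included, grouped by the pathway started.
2. Analyse SO6 and SO7 in this set. Analyse SO5 among its operated patients, since others have no trial construct to replace.
3. Count events in harvest-only patients from the date of harvest. Table 1 measures its time points from surgery, which these patients do not have.
4. Do not use PP for SO5, SO6 or SO7.
5. Keep mFAS and PP for efficacy, define what counts as having received treatment, and reconcile both sets with the ITT analysis promised in the Discussion.

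The cost is one additional analysis set and a few sentences. No trial procedure changes.

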## 4. Discussion

There is a lack of multicentric, randomized clinical trials in the literature, capable of defining the value of current regenerative medicine strategies based on MSCs. Bone healing in difficult clinical settings has gathered multiple early trials with cell therapy, but the available evidence is limited.

Nonunions after long bone fractures are a challenging scenario to evaluate the efficacy of cell therapy or other competing technologies. Furthermore, the severity of the included cases may impact the results. Delayed unions of the tibia were healed by bone marrow MSCs and platelet-rich plasma [25], but obviously the severity of the cases was limited. Clinical trials on the treatment of long nonunions frequently include any type of nonunion, from hypertrophic to oligotrophic or atrophic, and the results may be impacted by the case mix. A reference multicentric trial [8] included 25% atrophic nonunions in the control arm versus 42% in the experimental arm. To solve this issue, our trial will exclude hypertrophic nonunions.

The control arm in comparative trials about bone healing is a difficult choice. Although iliac crest autograft has long been considered the standard augmentation to obtain bone healing, this control may be variable due to the patient and the surgical variability. Besides, no reference studies are available about the effectiveness of ICA to support bone healing in nonunions. Recent data can only be obtained from its use as controls in other studies [8, 26], but the variability in the obtention of ICA and the subsequent complications [7, 27, 28] foster the proposal of alternatives. We used this information to quantitatively estimate the expected healing rates with ICA, although it may vary depending on the type and location of the nonunion.

The use of cultured hBM-MSCs associated with biomaterials to heal long bone nonunions has long been reported. In 2007, Bajada et al. [29] healed a resistant tibial nonunion with 5 × 10^6^ BM-MSCs combined with calcium sulphate (CaSO_4_) in pellet form. Giannotti et al. [30] treated 8 upper limb nonunions with expanded MSCs and autologous plasma gel with CaCl_2_. Ismail et al. [31] ran a clinical trial on 10 patients with atrophic nonunions randomizing 5 patients to 15 million autologous BM-MSCs, hydroxyapatite granules, and internal fixation, with 5 controls with ICA. Larger defects were also treated by these techniques. Marcacci et al. [32] reported 4 patients with diaphyseal bone defects treated with 20 × 10^6^ expanded BM-MSCs combined with cylinders of 100% porous hydroxyapatite, with bone healing. Dilogo et al. [33] reported a case of segmental tibial defect treated with 50 × 10^6^ BM-MSCs, hydroxyapatite (HA) granules, and bone morphogenic protein 2 (BMP-2). Therefore, proofs of concept are published and feasibility is confirmed by numerous authors, although the consensus is that controlled randomized clinical trials will have to clarify definitively the effectiveness and the cost/benefit superiority of the tissue engineering approach compared to other methods of bone reconstruction [29–33].

The dose of expanded cells in previously published studies is highly variable, partly dependent on the available technology. In a previous project (FP7-REBORNE), the current IMP was developed and approved for clinical trials (EudraCT 2011-005441-13 and EudraCT 2012-002010-39), and the attained dose covered the requisites of the current trial, that is 200 million cells, expanded from 25–35 mL of bone marrow. Currently, the optimum dose to heal nonunions in long bones is unknown. Maximizing the dose to be implanted has been the most frequent strategy in many ongoing declared trials. Our high dose (200 million cells) and even the low dose (100 million cells) compare favourably with previously published bone marrow-derived cell products checked for efficacy (15 million cells used by Ismail et al. [31], 20 million cells by Labibzadeh et al. [34]).

Difficulties are encountered to define the sample size, the randomization procedure, and the study design due to the scarcity of comparable studies. A multicentric, randomized study was planned to ascertain that, having standardized the ATMP in four countries (France, Germany, Italy, and Spain), patients could receive analogous treatment from different GMP facilities in different hospitals. First, this requires agreement of the national regulators, and a voluntary harmonization procedure (VHP) was launched within the European Union [35]. Second, stratification by production centre has been planned for the randomization procedure, and this will enable to similarly assess cell production in all centres.

The sample size calculations have been based on success rates with ICA as the control on bone healing multicentric trials [8]. Scarcity of references (both for controls and technology under evaluation) is observed in the literature. Of note, no direct head-to-head comparison in a well-designed randomized clinical trial has been previously conducted with ICA and MSCs. In this scenario with uncertainties in the final success rates and in the final delta of superiority, it is also noted that very small rate changes in those assumptions may have an impact in the actual statistical power. However, clinical relevance of the potential superiority of the technique would not be clearly defined unless the success rate is clearly higher. Furthermore, other reasons for failure besides the augmentation with the ATMP need to be excluded by the clinical trial committee. Foreseen reasons of failure unrelated to the ATMP include unstable fixation or other mechanical issues, inappropriate placement of the biomaterial with cells or the bone autograft (on-lay apposition instead of the recommended in-lay application), or intraoperative complications (intraoperative fractures or other distortion). Those cases will not be evaluated by PP although ITT analysis will be performed. Justification of the noninferiority of the lower versus the higher dose of hBM-MSCs is also a potential limitation of the study. A pragmatic approach was agreed in a noninferiority margin of 10% consolidation rate based on the differences between ICA controls and technologies designed to enhance bone healing in retrospective [26] and prospective [8] studies. This difference of 10% could be considered clinically irrelevant.

Unfortunately, many published studies and clinical trials on regenerative strategies to promote bone healing fail to include sufficient detail on the treated injuries and on the implanted cell product. This precludes interpretation of the outcomes and comparison among studies. Besides, variability may not permit other investigators to replicate the study conditions and results. To drive conclusions about the outcomes of a regenerative technology is then a challenge, given the complexity of biological therapies and the wide heterogeneity of conditions where bone regeneration is required.

This phase III clinical trial intended to clarify the role of bone regenerative therapies based on autologous cell expansion for nonunion of long bones; therefore, it stands as a standard for any GMP approach in this field. The interest of this study is driven by the treated condition, where the intrinsic potential of the fracture to heal seems surpassed; the cell product, with strong preclinical quality assessment and with strict release criteria to ensure reproducibility; and the study design, where an ambitious randomized comparison is intended to clarify the efficacy of cell therapy versus iliac crest autograft and the efficacy of a higher dose of 200 × 10^6^ expanded BM-MSCs to heal nonunions versus the lower dose of 100 × 10^6^ cells that may represent less cumbersome preparation of a more sustainable cell production. The results will possibly lead to a better understanding of the clinical application of stem cell technology.

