### 2.3. Patient Population and Evaluation

Each investigator will enroll eligible patients into the trial (after obtaining the signature of the due informed consent adapted to each national regulation) and will enter patient data into the eCRF timely throughout the study. Inclusion and exclusion criteria are shown in Table 2. During the inpatient stay, recovery, and follow-up, all participants will receive conventional treatment.

A clinical trial committee, composed by three independent expert clinicians, will review and adjudicate the primary efficacy outcomes (bone consolidation) and other collected clinical outcomes, using prespecified definitions and methods described in the Clinical Event Committee Charter. Files for adjudication will be prepared and accordingly blinded prior to adjudication.

Blood samples will be obtained for routine blood tests, serology tests (HIV-, syphilis, HBV, and HCV), and bone turnover marker tests (bone-specific alkaline phosphatase (BAP), C-terminal propeptide of type I procollagen (PICP), osteocalcin N-terminal fragment (Midtact-OC), carboxyterminal cross-linked telopeptide of type I collagen (beta-CTX), osteoprotegerin (OPG), receptor activator of nuclear factor NF-kappa B ligand (RANKL)). Flow diagrams of the trial are shown in Figures 1 and 2.

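### The per-protocol set is described on three different bases, and one of them removes failures by attributed cause, so membership can depend on the outcome

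*Protocol article*

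**What the plan says.** Three places in the protocol article bear on who enters the PP set.

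- **Section 2.5.2.** After both types of surgery, "the surgical technique will be reevaluated postoperatively by the clinical trial committee, to confirm the predefined criteria of a satisfactory surgical procedure", so that the case can be validated for PP analysis. The criteria cover complications, "absence of major complications after the procedure (intraoperative fracture, deviation, inadequate reduction, or other surgical gestures or interventions" (with an exception for fibular osteotomy), sufficiency of graft or biomaterial, and fixation, the last by "detecting immediately after surgery what could be considered an unstable fixation or unstable nail or other suboptimal techniques".
- **Section 3.2.** PP is the mFAS less patients with major protocol deviations. The mFAS is all treated patients, and unknown consolidation counts as failure.
- **Section 4, Discussion.** Here "other reasons for failure besides the augmentation with the ATMP need to be excluded by the clinical trial committee". The list opens: "Foreseen reasons of failure unrelated to the ATMP include unstable fixation or other mechanical issues". It goes on to misplacement of the graft or composite and to intraoperative complications. It ends: "Those cases will not be evaluated by PP although ITT analysis will be performed".

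Section 2.3 describes a clinical trial committee of three independent clinicians who "will review and adjudicate the primary efficacy outcomes (bone consolidation") from files that are blinded beforehand. In Table 1, one of the three components of consolidation is that no nail, plate or full construct replacement has taken place.

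**The concern.** Section 2.5.2 asks whether the operation was done adequately, a question that can be answered for every patient before healing is known. The Discussion starts from failures and asks why they failed. A patient with imperfect fixation who does not heal is removed under that wording; nothing in the same text removes a patient with the same fixation who heals.

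The category of other mechanical issues has no limit in kind or time. It also overlaps the endpoint: a broken or loose implant that needs a nail or plate replacement is a failure under Table 1, and could equally be called mechanical and left out of PP. A late event of that kind would count against the arm in the mFAS and disappear from PP.

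At stake is the PP result for the primary superiority comparison, one of the two populations in which section 3.2 says the plan will be tested. Removing failures raises the success rate in any arm where it happens. If the shares differ between arms, the PP contrast is biased; if they are equal, a true difference shrinks.

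**Working it through.** **Inputs from section 3.1.1.** G1 rate 74%; expected gain 20 points, so 94% in G2; 36 versus 72 patients; one-sided alpha 2.5%; 5% loss; stated power above 80%.

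**The plan's own figure.** A two-proportion normal approximation with pooled variance gives 80.4% power at 36 versus 72, which agrees with the statement. After 5% loss (34 versus 68) it gives 78.3%. The article gives no figure for PP exclusions.

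**Assumption.** Let f be the share of an arm's failures removed from PP. The article gives no value, so the values below are illustrations.

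**Formula.** With true success rate p, the PP rate is q = p / [p + (1 − p)(1 − f)].

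**No true effect, p = 0.74 in both arms.**

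- f = 20%: 0.74 / (0.74 + 0.26 × 0.8) = 0.74 / 0.948 = 78.1%.
- f = 30%: 0.74 / (0.74 + 0.26 × 0.7) = 0.74 / 0.922 = 80.3%.
- f = 50%: 0.74 / (0.74 + 0.26 × 0.5) = 0.74 / 0.870 = 85.1%.

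Rejection rates below come from 200,000 simulated trials with random removal of the stated share of failures and a pooled z test at one-sided 2.5%.

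| Removed from G1 / G2 failures | PP rate G1 | PP rate G2 | Difference (points) | One-sided rejection |
|---|---|---|---|---|
| 0 / 0 | 74.0% | 74.0% | 0 | 2.8% |
| 30% / 30% | 80.3% | 80.3% | 0 | 2.8% |
| 10% / 30% | 76.0% | 80.3% | 4.3 | 7.8% |
| 20% / 50% | 78.1% | 85.1% | 7.0 | 14.8% |
| 50% / 20% | 85.1% | 78.1% | −7.0 | 0.3% |

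The test itself runs at 2.8% with no removal, so 2.8% is the reference for the other rows.

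**Planned effect, 74% versus 94%, equal removal.**

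- f = 25%: G1 0.74 / 0.935 = 79.1%; G2 0.94 / (0.94 + 0.06 × 0.75) = 0.94 / 0.985 = 95.4%; difference 16.3 points.
- f = 50%: G1 85.1%; G2 0.94 / (0.94 + 0.06 × 0.5) = 0.94 / 0.970 = 96.9%; difference 11.8 points, against a true 20.

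**The three bases side by side.**

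| Place | Basis for leaving PP | When it can be known | Depends on healing? |
|---|---|---|---|
| 2.5.2 | Predefined technical criteria | Postoperatively; fixation immediately after surgery | No, if applied at that time |
| 3.2 | Major protocol deviation | Not stated | Not by its wording |
| 4 | Reason for failure unrelated to the cell product | Only once failure is established | Yes, as written |

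The Discussion also offers an ITT analysis as the counterpart to PP. Section 3.2 defines no set of that name; it defines the mFAS.

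**The case against.** The strongest reply is that section 2.5.2 is the operative rule and the Discussion only explains why it exists. The reasons in the Discussion (fixation, placement, intraoperative events) largely match the criteria in 2.5.2, which cover both interventions and are not limited to failures. On that reading a healed patient with a technical fault would also leave PP, and no outcome dependence arises. This may well be what is intended. It stands as a reason not to claim that membership does depend on the outcome. It does not remove the conflict, because the Discussion is framed around failures and its mechanical category is wider than anything in 2.5.2.

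Four stronger readings are tempting, and the article does not support them.

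- **That later clinical complications remove patients from PP.** The wording "These criteria include absence of major complications after the procedure" suggests this on its own, but the examples that follow are mainly intraoperative or technical.
- **That the committee would know the arm when it adjudicates.** Judging sufficiency of graft or biomaterial might reveal it, but section 2.3 says the adjudication files are blinded, and the charter is not shown. Unblinding is only an inference.
- **That the filled-gap criterion falls harder on G2 because its volume is fixed.** Section 2.5.1 puts the usual autograft need at about 10 cc, Table 3 lists 10 cc for every arm, and any shortfall would be visible at surgery rather than through the outcome.
- **That the false-positive rate is inflated in favour of G2.** That needs unequal removal in one direction, for which the article gives no evidence.

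It is also fair to say that the mFAS keeps every treated patient. Which set is primary may be settled in the full protocol or analysis plan, so nothing here rests on its absence from the article.

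**Conclusion.** The point holds in a limited form. Sections 2.5.2, 3.2 and 4 give three bases for one analysis set, and the Discussion, followed as written, selects exclusions among failures by attributed cause. PP membership can then depend on the outcome; the article does not establish that it will.

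Neither size nor direction can be fixed from the article, since both rest on assumed removal shares. With no true effect, equal removal leaves the error rate essentially unchanged. Removal of 20% of G1 and 50% of G2 failures gives a spurious 7.0 points and about 15% one-sided rejection; the reverse pattern gives 0.3% and would hide benefit. With the planned effect, equal removal of half the failures cuts the PP difference from 20 to about 11.8 points, which works against a superiority claim.

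The mFAS analysis is unaffected, so this concerns the soundness of PP as a supporting analysis and not the trial as a whole. It should be corrected because the correction is cheap and the PP result would otherwise be hard to interpret in either direction.

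**What to change.** 1. Reconcile sections 2.5.2, 3.2 and 4 into one definition of PP. Set PP status for every patient, success or failure alike, from the predefined immediate postoperative technical criteria of section 2.5.2, and lock it before any follow-up outcome is seen.
2. Limit the complications criterion in section 2.5.2 to the intraoperative and technical events that it lists.
3. Remove exclusion by cause of failure from the Discussion. Report causes of failure, late mechanical ones included, descriptively in the mFAS.
4. Replace the reference to ITT with the defined mFAS.

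The cost is wording in the protocol, with matching text in the committee charter and analysis plan. The committee must complete its technical review earlier. Some late mechanical failures will stay in PP, which is the price of a set that does not depend on the outcome.
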